**Methods:**

The intervention mapping (IM) protocol was used in the planning and design of WOW. Focus group discussions and interviews with employees and managers identified the importance of addressing risk factors for CVD at the worksite. Based on the employees’ preference for individual counselling, and previous evidence of the effectiveness of this approach in the worksite setting, we decided to use motivational interviewing as part of the intervention strategy. Thus, as a cluster-randomised, controlled control trial, employees at increased risk for CVD (N = 928) will be assigned to a control or an intervention group, based on company random allocation. The sessions will include motivational interviewing techniques, comprised of two face-to-face and four telephonic sessions, with the primary aim to increase habitual levels of PA. Measures will take place at baseline, 6 and 12 months. Secondary outcomes include changes in nutritional habits, serum cholesterol and glucose concentrations, blood pressure and BMI. In addition, healthcare expenditure and absenteeism will be measured for the economic evaluation. Analysis of variance will be performed to determine whether there were significant changes in physical activity habits in the intervention and control groups at 6 and 12 months.

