Increase fruit and vegetable intake.	8. Employees aim to accumulate at least 30 minutes of physical activity on at least 5 days of the week.
	8. Employees aim to increase daily fruit and vegetable intake to 5 servings or more per day.
	9. Employees list and choose a variety of fruit and vegetables that they might enjoy.
	10. Employees develop strategies and ideas with the wellness specialist to prepare their food/meals (and not to buy fast food/take out meals).

The work environment also inhibited physical activity, as employees spent most of their time sitting. One environmental barrier identified was seasonality, as employees interviewed indicated that they would not be prepared to exercise outdoors during the winter months, when the sun set earlier. Employees felt that they generally followed healthier diets during summer, when their intake of salads was higher, and there was a greater variety of fruit and vegetables.

Thus, the main objectives of the intervention are to increase habitual levels of moderate and vigorous intensity physical activity (to meet guideline of 150 minutes per week) and to improve dietary behaviour, specifically increased fruit and vegetable intake. The reduction in the totalnumber of risk factors will play a role in achieving the long-term goal of reduced risk and burden of cardiovascular disease.

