### Step 6: Evaluation plan

#### Study design

The intervention as developed in the previous steps will be evaluated in a cluster-randomised controlled trial in South African worksites with a 12-month follow-up. The two intervention groups will receive 6 counselling sessions over either a 3 or 6-month period, described in Table 3. The control group will receive usual care. These participants will be unaware of the other two groups participating in the research study.

**Table 3 T3:** Timeline and contact schedule for employees in the intervention groups

**Week**	**6-month intervention group**	**3 month intervention group**
0	Wellness day at company. (Baseline measurement)	Wellness day at company. (Baseline measurement)
1	Face-to-face contact	Face-to-face contact
	(set goals, action plan)	(set goals, action plan)
4	Telephone contact	Telephone contact
	(monitor progress)	(monitor progress)
8	Telephone contact	Telephone contact
	(monitor progress)	(monitor progress)
12	Telephone contact	Face to face (final contact)
	(monitor progress)	
16	Telephone contact (monitor progress)	
20	Telephone contact	
	(monitor progress)	
24	Face to face (final contact)	
	(set new goal, plan way forward)	
26	First follow up measurement	
52	Second follow up measurement	First follow up measurement Second follow up measurement

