#### Randomisation

Randomisation will take place at the company level, where participating companies will be assigned to either the intervention or the control group. The wellness specialists’ manager will assign each company with a number and then use a random numbers table to allocate the companies to either the intervention or control.

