### Statistical analyses

STATISTICA software package will be used for all the analyses (Stasoft, Inc. 184–199, Tulsa OK, SA) and intention to treat analysis will be performed for each of the outcomes. Mean, standard deviation and standard error will be calculated for the continuous variables. Frequency tables will be used to determine the percentage of individuals at risk. An Analysis of Variance (ANOVA) will be performed to determine whether there were significant changes in physical activity habits and nutrition in the intervention and control groups at 6 and 12 months.

The cost-effectiveness of the intervention programme will be determined from the societal and the employer perspective. Confidence intervals around differences in costs between the intervention groups and control group will be estimated using bootstrapping techniques. Cost effectiveness ratios will be calculated by dividing the difference between the mean total costs of the intervention groups and control group, by the difference in the mean habitual physical activity levels and total number of risk factors for cardiovascular disease. Uncertainty around the cost-effectiveness ratios will be graphically presented on Cost-Effectiveness planes (CE-planes) [34]. Furthermore, Cost-effectiveness acceptability curves will be estimated to show the probability of cost-effectiveness at different ceiling ratios [35].

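### Companies are randomised, but the only test named for physical activity and nutrition is an ANOVA with no company term and no stated between-arm contrast

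*Protocol article*

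**What the plan says.** The Study design section says that the intervention "will be evaluated in a cluster-randomised controlled trial in South African worksites with a 12-month follow-up". The Randomisation section fixes the unit: "Randomisation will take place at the company level, where participating companies will be assigned to either the intervention or the control group".

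Outcome measures makes change in habitual daily physical activity the primary outcome. Statistical analyses gives one inferential method for it: "An Analysis of Variance (ANOVA) will be performed to determine whether there were significant changes in physical activity habits and nutrition", and the sentence goes on "in the intervention and control groups at 6 and 12 months". The Methods paragraph of the abstract repeats this: "Analysis of variance will be performed to determine whether there were significant changes in physical activity habits in the intervention and control groups". Neither place mentions company.

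Sample size calculation takes 50% against 40% of employees not meeting the activity guideline, 80% power and a significance level of 0.05. It arrives at 775 employees at 12 months, 387 per group. It mentions no design effect, ICC or number of companies.

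For costs, by contrast, a between-arm difference is named: "Confidence intervals around differences in costs between the intervention groups and control group will be estimated using bootstrapping techniques". The unit to be resampled is not stated.

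**The concern.** Employees of one company share management, working hours, site and wellness staff, so their outcomes are likely to be correlated. When whole companies are allocated, the variation between companies is part of the error of the treatment comparison. An ANOVA whose error term is the variation between employees leaves that part out. Its standard errors are then too small and its false-positive rate exceeds the nominal level. The Discussion paragraph of the abstract says the results are meant to inform health care funders who would implement the programme, so a spurious positive finding would have consequences.

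The second issue is the contrast. The sentence asks whether there were changes in the groups, not whether the changes differ between them. Only the latter is protected by randomisation. If the sentence were carried out as a separate before-after test in each arm, a significant change in one arm and not in the other could be taken for an effect.

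**Working it through.** **1. Reproduce the plan's sample size.** Inputs from Sample size calculation: p1 = 0.50, p2 = 0.40, power 80%, alpha 0.05 (taken as two-sided; the article does not say). The usual formula for two independent proportions, with mean proportion 0.45, is

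n per arm = [1.960 × √(2 × 0.45 × 0.55) + 0.842 × √(0.50 × 0.50 + 0.40 × 0.60)]² / 0.10²
= [1.379 + 0.589]² / 0.01 ≈ 387.3.

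Twice that is about 774.7, so 775 in total (776 if each arm is rounded up to 388). The stated 775 is therefore the figure for independent employees, with a design effect of 1. The alternatives tried fit less well: 769 with unpooled variance, 816 with continuity correction, 610 one-sided.

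**2. Type I error if company is ignored.** The article gives no ICC and no number of companies, so both are assumed: ICC 0.005 to 0.05, and k = 4 to 20 companies of equal size per arm. With m = 387/k analysed per company:

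DE = 1 + (m − 1) × ICC; true type I error = 2 × [1 − Φ(1.96/√DE)].

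Example, k = 8 and ICC 0.01: m = 48.4, DE = 1 + 47.4 × 0.01 = 1.47, 1.96/√1.47 ≈ 1.61, type I error 0.106.

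| Companies per arm | Analysed per company | ICC 0.005 | ICC 0.01 | ICC 0.02 | ICC 0.05 |
|---|---|---|---|---|---|
| 4 | 96.8 | 0.107 | 0.161 | 0.251 | 0.415 |
| 8 | 48.4 | 0.078 | 0.106 | 0.160 | 0.286 |
| 15 | 25.8 | 0.065 | 0.079 | 0.109 | 0.190 |
| 20 | 19.4 | 0.061 | 0.072 | 0.094 | 0.157 |

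DE runs from 1.09 to 5.79 and the type I error from 6% to 42%.

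**3. Check by simulation.** A one-way ANOVA on individual change scores was simulated with no true effect (4,000 replicates per setting). At ICC 0.01, 0.02 and 0.05 it rejected in 16%, 25% and 42% of trials with 4 companies per arm, in 10%, 16% and 28% with 8, and in 8%, 11% and 19% with 15. A t-test on company means in the same data rejected in 4.5% to 5.6%.

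**4. Consequence for power.** With 387 per arm and a comparison that allows for company (effective size 387/DE), power for 50% against 40% is 76% at best (20 companies per arm, ICC 0.005) and 21% at worst (4 per arm, ICC 0.05). At 8 per arm it is 64% at ICC 0.01 and 52% at ICC 0.02. Keeping m fixed and adding companies, the total analysed for 80% power is 774 × DE: 846 to 4,480 over the range, and 1,141 or 1,508 at 8 per arm with ICC 0.01 or 0.02. These figures use the normal approximation, so they are somewhat favourable when companies are few.

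**5. The contrast.** Suppose separate within-arm tests were used, both arms shared the same true change, and each test had power p to detect it. The chance that exactly one arm is significant is 2p(1 − p), treating the two tests as independent: 42% at p = 0.3, 50% at p = 0.5 and 32% at p = 0.8, with no difference between arms.

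**The case against.** The article does not list the terms of the ANOVA, an ANOVA can carry a nested company factor, and an article may leave detail to an analysis plan that is not shown. It is therefore not proven that company will be ignored. This stands as a reason to say that p-values would be too small if the test is run as written. It does not remove the point: the article names a method that, as named, does not match the design, and its sample size independently treats the employee as the unit.

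A reader might go further and infer that no randomised comparison will be made. The text does not support that. One ANOVA over groups and times is a natural reading of the sentence. The pilot is reported with a group and time effect, the trial is sized on a between-group difference, controls are measured at the same times, and the cost-effectiveness ratios use between-group differences in mean activity. What remains is a fault of wording.

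Regression to the mean after selection for high risk, and season ("One environmental barrier identified was seasonality", reported from employee interviews), might also be raised as biases. Both would mislead only if within-arm changes were read as effects. A parallel between-arm comparison is protected against them, and a 12-month change compares the same time of year.

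Nor can it be said that the cost intervals are too narrow. The resampling unit is not given, and that detail is commonly left to an analysis plan. Leaving out the baseline value or city as covariates is a choice about efficiency, not an error, since the primary outcome is already a change.

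**Conclusion.** The point holds on clustering and, as a matter of wording, on the contrast. The trial allocates companies, while both the named test and the sample size treat employees as independent. For any positive ICC, the ANOVA as written has a type I error above 5%. The direction is certain, but the size cannot be fixed from the article. The range of about 6% to 42% rests on assumed ICCs of 0.005 to 0.05, 4 to 20 companies of equal size per arm, and 387 analysed per arm. The missing between-arm contrast needs correcting in the text, but it is not evidence that the comparison will not be made. This should be settled before analysis, because it concerns the validity of the primary test.

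**What to change.** State the primary analysis as the between-arm difference in physical activity at 6 and 12 months, accounting for company in one of two ways:

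- a mixed model with a random company effect and small-sample degrees of freedom (for example Kenward-Roger); or
- an analysis of company means, such as a t-test with companies as the observations.

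Adjustment for the baseline value is preferable in either case. For the proportion meeting the guideline, use a mixed logistic model or GEE with a small-sample correction. Say how the 3-month and 6-month intervention groups enter the contrast, since Study design describes both while Randomisation speaks only of intervention and control. State that changes within an arm will not be used as evidence of effect. If costs are bootstrapped, resample companies within arm.

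The cost is analysis wording and some programming, with no new data. The intervals will be wider. The stated 80% power holds only without clustering, so it must be restated with an explicit ICC and number of companies. That may show the planned 775 completers to be too few.

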#### Study population

Over the course of two months, all employees from the eligible companies will be invited to participate in the wellness day(s) of their company. The health insurer will offer and conduct a Health Risk Assessment of risk factors, including: family history, Body Mass Index (BMI) and body fatness, blood pressure and finger-prick cholesterol and glucose concentrations, self-report physical activity and dietary intake behaviour, smoking, and stress, to the employees at the wellness day.

Those employees who are identified to be at ‘increased’ or ‘high’ risk for CVD, based on an adapted Framingham score of 10% or more [18] will be invited by the wellness specialists (via telephone call) to take part in the research study. Employees agreeing to participate will be asked to sign an informed consent and to provide their email address and contact details.

Because all the companies hosting wellness days in this research study are clients of a major national health insurer, it will be able to access data for employees who do not volunteer for the screening activities, and thus be able to compare responders to non-responders. Recorded data for all employees include healthcare expenditure and whether they participated in a health screening activity recently. The data for the employees who choose not to participate will be sent to the researchers without any personal identifiers, thus ensuring employee confidentially. Being able to describe the non-responders is one of the strengths of this study design, and the insured population with whom we are working, providing insight into the problem of selection bias.

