#### Inclusion and exclusion criteria for companies

Companies with 300 or more employees will only be selected from those willing to allow a repeat of the HRA onsite at 6 and 12 months follow-up. In addition, the employer should have employee absenteeism data from their employee records available.

One of the challenges with worksite health promotion programs is that the company management should “buy in” to the intervention and support its implementation, and also “buy in” to the study and be willing to being placed in the wait-list control arm of the study. These issues will be discussed with the company during recruitment. To emphasize the importance of continued support, we require a letter of commitment from the management of prospective companies for the duration of the study. Furthermore, the researchers will invite participation and seek approval from the respective unions and health and safety committees functioning at the companies.

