### Outcome measures

The primary outcome of this study is a change in level of habitual daily physical activity. Secondary outcomes include: changes in dietary intake and Body Mass Index. Further, the secondary outcome measures include changes in the cardiovascular disease risk profile, which will be defined by the adapted Framingham score, incorporating blood pressure, total blood cholesterol, and smoking status. Data will be collected at baseline and at 6 and 12 months.

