#### Costs

The intervention costs that will be included are the cost of the wellness days screening, training of counsellors, employment costs of counsellors, opportunity cost that may be lost if employee’s sessions are during working hours, health promotion materials, travel and telephone calls. These data will be obtained from the health insurer who will keep records of all expenses related to the intervention, which includes the duration of counselling sessions.

Direct health care costs will be based on health-related claims data linked to doctors visits, hospitalisation and chronic medication will be obtained from the medical insurer. Indirect costs include costs for loss of productivity (i.e. sickness absenteeism). Absenteeism data will be obtained from the company Human Resource manager in each company. In addition, participants will keep a medical costs and absenteeism diary and submit it to the research team every 3 months.

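### The cost-effectiveness ratio is defined on differences in mean costs and mean levels with no baseline adjustment stated, although activity is measured at baseline and cost and absence records are already held

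*Protocol article*

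**What the plan says.** The Statistical analyses section of the protocol article gives the ratio in one sentence. The numerator comes from "dividing the difference between the mean total costs of the intervention groups and control group", and the result is divided "by the difference in the mean habitual physical activity levels and total number of risk factors for cardiovascular disease". I read the denominator as two effects and hence two ratios. On uncertainty, the same section says: "Confidence intervals around differences in costs between the intervention groups and control group will be estimated using bootstrapping techniques". It mentions no baseline value, change score or covariate for costs or effects.

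The Outcome measures section describes the effect differently: "The primary outcome of this study is a change in level of habitual daily physical activity". That section schedules data at baseline, 6 and 12 months, and Table 3 places the baseline at the week-0 wellness day.

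The Costs section names the sources. For health care: "Direct health care costs will be based on health-related claims data linked to doctors visits, hospitalisation and chronic medication". Absence comes from each company's Human Resource manager. In addition, "participants will keep a medical costs and absenteeism diary and submit it to the research team every 3 months". No period is given for claims or for Human Resource absence data, either before the wellness day or after it.

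Two other sections bear on what could be available. Under Study population, on the insurer's data: "Recorded data for all employees include healthcare expenditure and whether they participated in a health screening activity recently". Under the criteria for companies: "the employer should have employee absenteeism data from their employee records available".

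**The concern.** Allocation is by company (Randomisation section), and the number of companies is not stated. Companies can differ beforehand in claims, sick leave and activity. With few of them, such differences may not average out well in a single allocation. An estimator with no baseline term leaves in the numerator and denominator whatever part of a starting difference persists to follow-up.

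A ratio is sensitive to this when the effect in its denominator is small. The cost-effectiveness plane and the acceptability curve are built on the same differences, so they inherit any shift. The economic evaluation is a stated aim (Background), and the Abstract presents it as important to the health care funders who would implement the programme.

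The wording also puts the effect in the ratio on a different scale (mean level) from the primary outcome (change), with no reason given.

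**Working it through.** **1. Sections side by side.** Effects: the primary outcome is a change with a baseline value, while the ratio is written on levels with no baseline. Costs and absence: the diary and the log book run from enrolment. Claims and Human Resource records have no stated period, but they are held independently of the trial. An adjusted analysis is therefore feasible for the effects from data already planned. It is probably feasible for costs and absence from the named sources. The text states neither.

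**2. The plan's own sample size, used as input.** For 50% versus 40%, two-sided 0.05, 80% power, pooled variance, no continuity correction:

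n = [1.96·√(2·0.45·0.55) + 0.842·√(0.50·0.50 + 0.40·0.60)]² / 0.10² ≈ 387.3, which rounds up to 388 per group.

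The plan states 387 per group and 775 in total, so its figure reproduces to rounding. I use 387 per arm.

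**3. Chance baseline difference in activity.** Inputs: SD 120.9 min/week and mean 63.0 min/week (pilot, Table 2); 387 per arm (Sample size calculation). Assumptions: 50 employees per company; ICC 0, 0.01 or 0.05.

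SE = 120.9·√(2/387 · DE), with DE = 1 + (50 − 1)·ICC.

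| ICC | DE | SE (min/week) | 1.96·SE |
|---|---|---|---|
| 0 | 1.00 | 8.7 | ±17 |
| 0.01 | 1.49 | 10.6 | ±21 |
| 0.05 | 3.45 | 16.1 | ±32 |

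**4. Sensitivity to the number of companies.** With k companies per arm (assumed), SE = 120.9·√(2·[ICC/k + (1 − ICC)/387]). The 95% ranges in min/week are:

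| k per arm | ICC 0.01 | ICC 0.05 | ICC 0.10 |
|---|---|---|---|
| 3 | ±25.7 | ±46.3 | ±63.3 |
| 5 | ±22.6 | ±37.4 | ±50.1 |
| 10 | ±20.0 | ±28.9 | ±37.2 |
| 20 | ±18.5 | ±23.6 | ±28.7 |

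**5. How much carries over.** With equal variances at baseline and follow-up and correlation r between the arm differences at the two times, a baseline difference d shifts the expected follow-up difference by r·d. For d of one SE, the shift runs from 0.3·8.7 = 2.6 min/week (r = 0.3, no clustering) to 0.7·16.1 = 11.3 min/week (r = 0.7, ICC 0.05). These values of r are assumptions.

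**6. What adjustment gains.** Relative to unadjusted levels, the variance of the arm difference becomes 1 − r² with covariate adjustment and 2(1 − r) with a simple change score:

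| r (assumed) | Covariate-adjusted | Change score |
|---|---|---|
| 0.3 | 0.91 | 1.40 |
| 0.5 | 0.75 | 1.00 |
| 0.7 | 0.51 | 0.60 |
| 0.9 | 0.19 | 0.20 |

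For costs, if prior-period and trial-period costs correlate at 0.3 to 0.6 (assumed), adjustment removes r² = 9% to 36% of the individual-level variance.

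**The case against.** The strongest reply is that the sentence is the textbook definition of a cost-effectiveness ratio and does not say how either difference is estimated. Baseline-adjusted means would satisfy it. The preceding paragraph of the same section speaks of changes in activity, so the reference to levels may be loose wording. A costing window is also a detail that a journal article commonly leaves to a fuller document.

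Much of this stands, and it rules out three stronger readings that a reader might draw.

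- **That the trial has no pre-intervention cost or absence data.** The Costs section states no window of any kind, so its silence about an earlier period proves nothing. The Study population section and the criteria for companies point to sources that could supply such data.
- **That the ratio uses raw follow-up values and discards the week-0 measurements.** The text says neither. It only fails to state an adjustment.
- **That differences between companies pass in full into the ratio as bias.** Companies are randomised, so prior differences balance in expectation, and carry-over depends on the pre-post correlation. Selection after allocation could add systematic imbalance, since unblinded wellness specialists make the invitation calls. But the article does not state whether allocation precedes those calls.

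The bootstrap intervals, planes and acceptability curves are meant to display sampling uncertainty. They do not remove an imbalance from the point estimate or recover the precision that adjustment would give.

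What survives is that the article goes as far as writing out the estimator, writes it on levels with no baseline term, and defines the primary outcome as a change. That is a stated choice that can be improved, not only an omitted detail.

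**Conclusion.** The point holds in a limited form. The ratio is defined without stated baseline adjustment, on a scale that does not match the primary outcome, in a trial that allocates companies and has or can reach the baseline data. The consequence is exposure to chance imbalance and avoidable loss of precision in the economic evaluation. The primary effectiveness comparison is not affected.

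The size is an illustration. The standard error of a chance baseline difference in activity is 8.7 min/week without clustering and 10.6 to 16.1 under the assumed ICCs and company size, against a pilot mean of 63.0. It rests on the SD of a convenience pilot sample and on 387 per arm with the two counselling schedules taken together. If each schedule is compared with control separately, its group is smaller and the standard error larger. No figure in the documents allows the resulting error in the ratio itself to be calculated, and none is claimed.

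**What to change.** 1. **Statistical analyses section.** Define each ratio as the baseline-adjusted difference in mean total costs over the baseline-adjusted difference in activity, and likewise for the number of risk factors. Use the week-0 health risk appraisal values as the effect baselines. Use covariate adjustment rather than simple change scores, which are less precise than unadjusted levels when r is below 0.5. Recompute the adjusted differences in each bootstrap sample, so that the intervals, planes and acceptability curves refer to the same estimator.
2. **Costs section.** State the costing window. Take a look-back of fixed length before each company's wellness day (for example the preceding 12 months) for claims and Human Resource absence, for every consenting participant in all groups and from the sources already named. Use it as the baseline for costs and absence.

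The cost is one additional retrospective extract, consent wording that covers the look-back, and a revised formula. Participants who joined the insurer or employer recently will have a shorter look-back, so the plan should say how their baseline is handled.
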